**Methods/Design:**

A community clinical trial is proposed, with a 1-year follow-up period, that is multicentric, controlled, parallel, and with randomized allocation of clusters in 20 health care centers within the Community of Madrid. The study's objective is to evaluate the effectiveness of a standard care intervention in primary health care (intervention CuidaCare) to improve the quality of life of the caregivers, measured at 0, 6, and 12 months after the intervention.

One hundred and forty two subjects (71 from each group) ≥65 years, identified by the nurse as the main caregivers, and who provide consent to participate in the study will be included.

The main outcome variable will be perceived quality of life as measured by the Visual Analogue Scale (VAS) of EuroQol-5D (EQ-5D). The secondary outcome variables will be EQ-5D Dimensions, EQ-5D Index, nursing diagnosis, and Zarit's test. Prognostic variables will be recorded for the dependent patient and the caregiver.

The principle analysis will be done by comparing the average change in EQ-5D VAS value before and after intervention between the two groups. All statistical tests will be performed as intention-to-treat. Prognostic factors' estimates will be adjusted by mixed-effects regression models. Possible confounding or effect-modifying factors will be taken into account.

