## Methods/Design

### Study design

A community, controlled, multicentric clinical trial with randomized allocation by clusters and a 1-year follow-up period.

The intervention will be carried out by voluntary nurses with at least 3 years of experience in primary care, from 20 primary health care centers (PHCC) in the Community of Madrid (Spain).

The randomized unit will be the PHCCs (clusters). The analysis unit will be the caregiver (check-list cluster CONSORT in Additional file 1).

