### Sample size

Sample size has been calculated considering a relevant post-intervention average difference of 15 points between the intervention and control groups measured on the EQ-5D VAS, and a standard deviation of 25 (estimation obtained from Roset et al. [26]). This difference is equivalent to an effect size of 0.6.

Assuming an alpha error of 0.05 and a beta error of 20%, 44 caregivers are necessary for each group.

Since randomization is done by clusters, the sample size is adjusted in order to take into account the design effect. We have considered an intraclass correlation coefficient of 0.02 [27] and assumed an average cluster sample size of 15 caregivers. The design effect is 1.28. With these assumptions and expecting a 20% loss to follow-up after a 1-year period, the required sample size is 142 (71 caregivers per group).

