#### *Sequence generation*

The 20 PHCCs will be allocated into intervention or control groups by using a stratified randomizing sequence by number of caregivers, generated by a computer (EPIDAT 3.1).

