### Analysis

1. Descriptive analysis of each variable with its corresponding 95% confidence interval (CI). Tests for normality. Description of the profile of patients who abandon the study, and their reason for withdrawal.

2. Comparison of the group at the beginning of the trial for response variables, descriptive variables, and prediction factors. Bivariate, statistical, and other tests appropriate for the type of variable (qualitative or quantitative) will be used.

3. Analysis of primary outcome at the end of the intervention (0 month of follow-up period), and at 6 and 12 months after the intervention. The average change in EQ-5D VAS value before and after the intervention will be compared between the two groups by using parametric and/or non-parametric tests and the CI of the difference will be calculated. A mixed-effects regression model will be used to adjust by prognostic factors. Confounding factors or factors that may alter the recorded effect will be taken into account in this analysis.

4. Analysis of secondary outcome. For each of the secondary response variables, the variable outcomes will be compared based on the assigned group by calculating the difference of means or proportions of each variable, as well as CIs.

All statistical tests will be performed as intention-to-treat. The last and baseline observations carried forward will be used for missing data. Significance will be set at p < 0.05.

Researchers in charge of performing the analysis will not know which intervention has been assigned to each of the included patients.

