## Discussion

Systematic reviews of studies [14-17] evaluating the effectiveness of interventions and caregiving strategies for the caregiver show methodological limitations in their conclusions, mainly related to insufficient sample sizes, high losses to follow-up of subjects, and follow-up period duration. They also reveal the variability of the interventions and outcome variables employed.

The CuidaCare intervention is a personal intervention, aimed at both the caregiver and the dependent patient, and based on coping techniques.

The design selected for this project is the best possible given the intervention, while seeking to avoid possible contamination effects among centers. The number of clusters is sufficient for the randomization to balance potentially confounding factors among themselves and we consider modelization techniques which take into account the intracluster correlation.

Given the nature of the intervention, it cannot be masked. However, we have designed a blind evaluation of the outcome.

Subjects will be recruited for the study by their own nurses. This increases variability, which we attempt to minimize by training all participating nurses on the one hand, and by creating a research protocol and implementing an electronic data collection notebook on the other hand.

Of note, the fact that nurses recruit their own patients increases implementation in standard practice.

Participation of nurses is voluntary. We are aware that a bias is introduced, but they are motivated and engaged professionals who will facilitate the development of innovative interventions such as CuidaCare.

Despite loses to follow-up in primary care being minimal as a result of the user's proximity to the system and the possibilities the health professional has to contact relatives and friends, we have estimated a high percentage in the trial due to the high morbidity-mortality of dependent patients, which will force the caregiver to abandon the trial due to the patient's hospitalization or death.

The design of the trial is pragmatic, which will allow evaluating not only its effectiveness, but also its applicability in the context of primary care.

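### The comparison named as principal, and its confidence interval, are not tied to an analysis that allows for randomisation by health centre

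*Protocol article*

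**What the plan says.** All references are to the protocol article.

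- **Study design:** "The randomized unit will be the PHCCs (clusters). The analysis unit will be the caregiver".
- **Abstract, Methods/Design:** "The principle analysis will be done by comparing the average change in EQ-5D VAS value before and after intervention between the two groups".
- **Analysis, item 3:** the mean change in VAS "will be compared between the two groups by using parametric and/or non-parametric tests and the CI of the difference will be calculated". The next sentence reads "A mixed-effects regression model will be used to adjust by prognostic factors". No random effect for centre is named.
- **Analysis, item 4:** secondary outcomes are compared between groups "by calculating the difference of means or proportions of each variable, as well as CIs". No model is named.
- **Sample size:** ICC 0.02, average cluster size 15, design effect 1.28, 20% loss, 142 caregivers (71 per group).
- **Discussion:** "we consider modelization techniques which take into account the intracluster correlation".

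**The concern.** An ordinary two-group test, parametric or rank-based, takes every caregiver as an independent observation. Caregivers in one centre share nurses and setting, and the sample size calculation itself assumes that they are correlated. With any positive ICC, the ordinary test understates the standard error of the group difference, so its p-value is too small and its interval too narrow.

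The text does name the deciding analysis, and it is this two-group comparison. The mixed model comes afterwards and has a different job. Its grouping factor is also open: with three assessments after the intervention period, mixed-effects could mean a random effect for caregiver alone, which would not deal with centre. An analyst who follows the text literally would report as the main result a test that contradicts the planning assumption.

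At stake are the 5% significance level and the 95% coverage claimed for the primary outcome, and likewise for the secondary outcomes under item 4.

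**Working it through.** **Inputs.** From Sample size: difference 15, SD 25, alpha 0.05, beta 20%, ICC 0.02, cluster size 15, loss 20%, total 142. From Sequence generation: 20 centres. Sidedness is not stated; two-sided is assumed because it reproduces the plan's figure.

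**1. The plan's own sample size**

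- Per group before clustering: 2 × [25 × (1.960 + 0.842)/15]² = 43.6, rounded up to 44. This agrees with "Assuming an alpha error of 0.05 and a beta error of 20%, 44 caregivers are necessary for each group".
- Design effect: 1 + (15 − 1) × 0.02 = 1.28.
- 44 × 1.28 = 56.32; 56.32/0.80 = 70.4, rounded up to 71 per group, 142 in all.

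All three stated figures reproduce.

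**2. Caregivers per centre.** 142/20 = 7.1 recruited. After 20% loss, about 57 per group remain (0.8 × 71 = 56.8), and 114/20 = 5.7 per centre. The assumed 15 is about twice the size that the plan implies.

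**3. Error of a test that ignores centre** (normal approximation)

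DE = 1 + (m − 1) × ICC. Actual two-sided error = 2 × [1 − Φ(1.96/√DE)]. The correct interval is √DE times the unadjusted one.

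| Caregivers per centre (m) | ICC | DE | Type I error | Coverage | Correct interval wider by |
|---|---|---|---|---|---|
| 5.7 (after loss) | 0.02 | 1.094 | 6.1% | 93.9% | 5% |
| 7.1 (142/20) | 0.02 | 1.122 | 6.4% | 93.6% | 6% |
| 15 (plan's assumption) | 0.02 | 1.28 | 8.3% | 91.7% | 13% |
| 7.1 | 0.01 (assumed) | 1.061 | 5.7% | 94.3% | 3% |
| 7.1 | 0.05 (assumed) | 1.305 | 8.6% | 91.4% | 14% |
| 7.1 | 0.10 (assumed) | 1.61 | 12.2% | 87.8% | 27% |

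Only ICC 0.02 comes from the document.

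**4. Check by simulation.** With no true effect, 10 centres per group, 7 caregivers each and ICC 0.02, rejection at nominal 5% was 6.5% for the t-test on caregivers (20,000 runs), 6.7% for the rank test (5,000 runs) and 5.0% for a t-test on centre means (20,000 runs). Choosing the rank test does not help; an analysis that respects the centres does.

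**5. What the correct analysis costs in precision.** With 57 completers per group, 5.7 per centre and ICC 0.02:

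- Unadjusted half-width: 1.96 × 25 × √(2/57) = 9.2 points.
- With the design effect: SE = 25 × √(2 × 1.094/57) = 4.90; half-width 1.96 × 4.90 = 9.6 points.
- With a t reference on 20 − 2 = 18 degrees of freedom (critical value 2.10): 2.10 × 4.90 = 10.3 points.
- Power for 15 points (noncentrality 15/4.90 = 3.06): 0.86 by the normal approximation, 0.83 with 18 degrees of freedom.

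At the plan's more cautious design effect of 1.28, power by the normal approximation is 0.81.

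**The case against.** The strongest reply is that the plan does address clustering. The sample size is inflated for it, a cluster CONSORT checklist is cited, item 3 includes a mixed-effects model for the primary outcome, and the Discussion presents clustering-aware modelling as part of the design. In a trial randomised by centre, the natural grouping factor for a mixed model is the centre. The article is condensed, and details of random effects and degrees of freedom may stand in a fuller document.

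Much of this stands, and it rules out several stronger readings:

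- A reader might infer that the plan ignores clustering altogether. The documents do not support that; the fault lies in the comparison named as principal and in item 4.
- A reader might take the caregiver as analysis unit as proof that clustering is ignored. It is not: a mixed model with a centre effect also analyses caregivers.
- A reader might quote an error rate of 8% or more as the trial's error. That needs either 15 caregivers per centre, which 142 caregivers in 20 centres do not give, or an ICC above the documented 0.02.
- A reader might infer two competing primary p-values from the choice of parametric and/or non-parametric tests. Item 1 plans tests for normality, so the wording can mean a choice by distribution. It is loose, but a lesser and separate matter.
- Missing detail of the mixed model is not in itself a fault in an article.

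The reply does not reach the order of the analyses. The abstract and item 3 state which comparison is principal and give the mixed model another purpose. The Discussion sentence is general and does not say that the primary p-value and interval come from such a model. This is a stated choice that does not fit the design, not a detail left for later.

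**Conclusion.** The point holds in a limited form. Read literally, the deciding p-value and interval do not account for randomisation by centre, which is inconsistent with the ICC used for the sample size. The secondary comparisons in item 4 have the same weakness.

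The size is modest under the plan's own figures: a type I error of about 6.1% to 6.4% instead of 5%, with correct intervals about 5% to 6% wider. This rests on ICC 0.02, roughly equal centre sizes, a two-sided test and the normal approximation. The direction is anti-conservative for any positive ICC, and the size depends on an ICC that is only a planning value: at 7.1 per centre it would be about 8.6% if the ICC were 0.05. The correction should be made because it concerns the analysis that decides the trial and is cheap.

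**What to change.** Reword Analysis items 3 and 4, and the matching sentence in the abstract.

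- **Primary outcome:** state that the estimate, confidence interval and p-value come from one cluster-aware analysis. This can be the mixed model already planned, with a random intercept for centre, baseline VAS as a covariate and a small-sample degrees-of-freedom correction (Kenward-Roger or Satterthwaite) for 20 centres. A centre-level analysis is the alternative.
- **Simple two-group test:** keep it as descriptive only.
- **Secondary outcomes:** apply the same allowance for centre to differences of means and of proportions.

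Randomisation uses a "stratified randomizing sequence by number of caregivers", so the stratum is a sensible further fixed term; that detail can be left to the analysis plan.

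Cost: no extra data and, under the planning assumptions, no extra caregivers. Intervals widen by about 5% to 6% from the design effect, plus a further 7% (2.10/1.96) if 18 degrees of freedom are used.

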#### Secondary objectives

• Describe the socio-demographic profile of the dependent patient and the main caregiver.

• Describe the degree of burden for the main caregivers, measured with the Zarit's test.

• Compare the effectiveness of the CuidaCare intervention against the standard nursing practice for improving the caregiver’s quality of life, measured with the EQ-5D Dimensions and the EQ-5D Index, at the end of the intervention and during follow-up visits at 6 and 12 months.

• Compare the effectiveness of the CuidaCare intervention with standard nursing practice in reducing caregiver burden, as measured by nursing outcome NOC Indicators and Zarit's test at the end of the intervention and during follow-up visits at 6 and 12 months.

• Analyze socio-demographic factors, characteristics of the dependent patient, caregiving attributes, and formal support that characterize the quality of life of the main caregiver.

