### Data collection method

Information will be collected via a clinical interview and data will be recorded in an electronic data collection notebook specifically designed for this trial. Variables will be collected during 4 visits: at the beginning of the trial, at the end of the intervention, and at 6 and 12 months after the intervention. The timing for the data collection is shown in Table 1.

**Table 1 T1:** Procedures to be followed and information to be recorded at each patient’s visit

	
Step 1	Recruitment of caregivers
	- Presentation/information about the trial
	- Invitation to participate
	- Checking inclusion/exclusion criteria
	- Signing of informed consent
	- Collection of sociodemographic variables (dependent patient and caregiver)
Step 2	Primary health care center randomization
Step 3	Base-line visit
	Collection of variables on:
	- Dependent Patient: degree of cognitive deterioration and dependency level.
	- Evaluation of formal support.
	- Caregiver: self-perceived quality of life, degree of burden, evaluation of anxiety/depression degree, Apgar family test, and nursing diagnosis.
Step 4	Intervention period (duration of 6 months)

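### Item 4 of the analysis compares the secondary outcomes as plain group differences and names no use of the baseline value collected for each, which gives up precision

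*Protocol article*

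**What the plan says.** The abstract lists the outcomes concerned: "The secondary outcome variables will be EQ-5D Dimensions, EQ-5D Index, nursing diagnosis, and Zarit's test". The Secondary objectives are worded as effects on them, for example "Compare the effectiveness of the CuidaCare intervention with standard nursing practice in reducing caregiver burden".

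Under Data collection method, "Variables will be collected during 4 visits: at the beginning of the trial, at the end of the intervention, and at 6 and 12 months", the later two counted from its end. The baseline row of Table 1 (Step 3) includes "Caregiver: self-perceived quality of life, degree of burden, evaluation of anxiety/depression degree, Apgar family test, and nursing diagnosis", and the three follow-up rows repeat these items. Each secondary outcome named in the abstract therefore has a baseline value.

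The Analysis section handles the two tiers of outcome differently:

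- Item 3, primary outcome: "The average change in EQ-5D VAS value before and after the intervention will be compared between the two groups". It adds: "A mixed-effects regression model will be used to adjust by prognostic factors".
- Item 4, secondary outcomes: "the variable outcomes will be compared based on the assigned group by calculating the difference of means or proportions of each variable, as well as" confidence intervals. No baseline term and no model appear.

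Item 2 compares the groups at baseline on the response variables, but nothing carries that comparison into the item 4 estimate.

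**The concern.** Burden or utility at follow-up probably depends on where the caregiver started. A comparison that leaves out the starting value keeps this predictable variation in the error term, so its interval is wider than it needs to be. With 20 centres randomised and 71 caregivers per group, the groups can also differ by chance at baseline. Part of that difference then appears in the follow-up contrast.

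At stake are the precision of the secondary results and how they are read. If a baseline imbalance in Zarit is seen and no adjustment was specified, any adjustment made later looks chosen after the fact.

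**Working it through.** **Inputs from the Sample size section.** Difference 15, SD 25 ("This difference is equivalent to an effect size of 0.6"), alpha 0.05, power 80%, intraclass correlation 0.02, 15 caregivers per cluster, 20% loss. Alpha is taken as two-sided, which reproduces the stated figure.

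**The plan's own figure.** n per group = 2 × [25 × (1.96 + 0.84) / 15]² = 43.6, rounded up to 44. Design effect = 1 + 14 × 0.02 = 1.28. Then 44 × 1.28 = 56.32, and 56.32 / 0.80 = 70.4, rounded up to 71 per group, 142 in total. The stated figure reproduces. It concerns the VAS only. The protocol gives no effect size, SD or power for a secondary outcome.

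**Precision.** Let r be the correlation between baseline and follow-up. The protocol gives none, so the range below is an assumption. Variances are relative to the plain follow-up difference. Adjustment for baseline gives 1 − r², and a change score gives 2 − 2r.

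| r (assumed) | Follow-up only | Baseline-adjusted | Change score | Interval narrowed by adjustment, 1 − √(1 − r²) |
|---|---|---|---|---|
| 0.3 | 1.00 | 0.91 | 1.40 | 5% |
| 0.5 | 1.00 | 0.75 | 1.00 | 13% |
| 0.7 | 1.00 | 0.51 | 0.60 | 29% |

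The variance saved by adjustment is therefore 9%, 25% and 49%. Adjustment is at least as precise as either alternative throughout.

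**Power, as illustration only.** Effective n per group = 71 × 0.8 / 1.28 = 44.4. Power = Φ(0.6 / √(1 − r²) × √(44.4 / 2) − 1.96). This gives 81% unadjusted, and 84%, 90% and 98% at r = 0.3, 0.5 and 0.7. The 0.6 is borrowed from the VAS.

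**Chance imbalance.** The SE of the baseline difference is √(2 × 1.28 / 71) = 0.19 SD, so the chance that an imbalance exceeds 0.2 SD in either direction is about 29% per outcome. With 142 / 20 = 7.1 caregivers per centre, the design effect is 1 + 6.1 × 0.02 = 1.12, the SE is 0.18 SD and the chance is 26%. An imbalance of 0.2 SD shifts the unadjusted follow-up difference by r × 0.2 SD, which is 0.06, 0.10 or 0.14 SD at the three values of r.

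These formulas suit the Zarit score and EQ-5D Index. For nursing diagnosis and EQ-5D Dimensions they are only a rough guide.

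**The case against.** Four counter-arguments deserve an answer.

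**Item 4 is one condensed sentence, and covariates belong in the SAP.** It is true that item 4 does not forbid adjustment and could loosely be read as a difference of mean changes. But it states a method, directly below an item that spells out change and a model for the primary outcome. The abstract's remark on mixed-effects adjustment and the Discussion's remark on intracluster correlation are general, and neither assigns a baseline covariate to a secondary outcome. The point therefore stands as an improvement to a stated method.

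**The unadjusted difference is not wrong.** This stands in full. A reader might infer that item 4 biases the secondary results, or that an imbalance in Zarit would yield a false finding beyond the nominal error rate. The documents do not support that. Averaged over randomisations the difference is unbiased, and a correctly computed interval already allows for chance imbalance. What remains is lost precision and error conditional on the imbalance that occurs.

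**Item 3 is no better model to copy.** A reader might infer that item 4 is weaker than the change score in item 3. By the table, that is untrue for r below 0.5, where the change score has the larger variance. Nor does item 3 state a random centre effect, so a reference back to its model would not settle the clustering.

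**Adjustment has its own risk.** Table 1 puts centre randomisation (Step 2) before the baseline visit (Step 3), and the Masking section covers only post-intervention measurement. A baseline recorded with knowledge of allocation could bring bias into an adjusted estimate, most plausibly for the nurse-judged diagnosis. This stands, and it is why the unadjusted result should be shown too.

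**Conclusion.** The point holds as one of efficiency. Item 4 names no use of baseline values that the trial collects, and a more precise analysis is available. For continuous outcomes the variance reduction is about 9%, 25% or 49% if r is 0.3, 0.5 or 0.7. The values of r are assumed, because the protocol gives none. At the low end the gain is small: 81% to 84% power in the illustration.

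The power figures should not be read as the power of the secondary analyses, since the effect size behind them is the VAS one. The primary analysis and the sample size of 142 are unaffected. This is a worthwhile, inexpensive amendment and not a defect that threatens the trial's conclusions. The absence of any clustering allowance in item 4 is a separate matter, which the wording below happens to cover.

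**What to change.** Amend item 4 along these lines:

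> Zarit score and EQ-5D Index at each follow-up will be compared between groups in a mixed-effects model with a random effect for health care centre and the baseline value of the same outcome as covariate. Nursing diagnosis and EQ-5D Dimensions will be analysed in the corresponding model for binary or ordinal outcomes, with a random centre effect and adjustment for baseline status. Adjusted group effects will be reported with 95% confidence intervals. Unadjusted differences in means or proportions will be reported beside them as descriptive or sensitivity results.

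State the centre effect explicitly, since item 3 does not name it. Add a sentence acknowledging that baseline measurement follows centre randomisation without stated masking, so that adjusted and unadjusted results are read together, above all for nursing diagnosis.

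The cost is one paragraph of analysis text and somewhat more modelling. No new data, visits or participants are needed.

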### Withdrawal criteria

Main caregivers who, once recruited, sicken of a severe pathology.

Main caregivers of dependent patients who are hospitalized for more than 3 months over the trial period.

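### Carry-forward is the only stated handling of missing VAS values, although the expected 20% loss comes from events likely to change the caregiver's self-rated health

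*Protocol article*

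**What the plan says.** The Analysis section of the protocol article compares the mean change in EQ-5D VAS between groups ("The average change in EQ-5D VAS value before and after the intervention will be compared between the two groups") at three times: "Analysis of primary outcome at the end of the intervention (0 month of follow-up period), and at 6 and 12 months after the intervention". It adds "All statistical tests will be performed as intention-to-treat" and then, for missing values, "The last and baseline observations carried forward will be used for missing data". It does not say when the last value applies and when the baseline value does, and it names no sensitivity analysis. A mixed-effects model is planned, but only to adjust for prognostic factors.

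Three other places bear on the rule:
- Sample size: the calculation was made "expecting a 20% loss to follow-up after a 1-year period".
- Discussion: a high percentage of loss is foreseen because of illness and death among the dependent patients, "which will force the caregiver to abandon the trial due to the patient's hospitalization or death".
- Withdrawal criteria: "Main caregivers who, once recruited, sicken of a severe pathology" are withdrawn, as are caregivers whose patient is in hospital for more than 3 months.

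**The concern.** The outcome is the caregiver's own rating of health. The protocol's reasons for loss (a death, a long hospital stay, a severe illness of the caregiver) are occasions when that rating is unlikely to stand still. Baseline carried forward sets the change to exactly zero. Last observation carried forward freezes the rating at a visit before the event. The protocol does not call the loss informative. That is an inference from its stated reasons, but a strong one.

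At stake are the size of the primary estimate, which the Hypothesis section sets against a 15-point threshold, and the amount of information the analysis claims to have. The protocol states the rule outright, so this is not a detail left to a later analysis plan.

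**Working it through.** **Inputs from the Sample size section:** difference 15, SD 25, alpha 0.05 (two-sided reproduces the figure), power 80%, ICC 0.02, cluster size 15, loss 20%.

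**The plan's own figure.** The two-sample formula gives 43.6, so 44 per group. Design effect = 1 + (15 − 1) × 0.02 = 1.28. 44 × 1.28 = 56.32, and 56.32 / 0.8 = 70.4, so 71 per group and 142 in total. It reproduces.

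**Where the two rules differ.** At the end of the intervention the only earlier value is baseline, so both rules impute zero change. At 6 and 12 months they differ for any caregiver who has an earlier follow-up value.

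**Bias, baseline carried forward.** With loss d_I and d_C, the expected estimate is (1 − d_I) × change_I − (1 − d_C) × change_C, if those lost would have had the same mean change as those seen.
- 20% in each arm: 0.8 × 15 = 12.0.
- Assumed loss of 10% and 30%, either way round, with an assumed control change of −10 to +5: from 0.7 × 20 − 0.9 × 5 = 9.5 to 0.9 × 20 − 0.7 × 5 = 14.5.

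**Standard error, baseline carried forward.** Take 25 as the SD of change, which assumes a correlation of 0.5 between visits, and no change in the control arm.
- Variance, intervention: 0.8 × 625 + 0.8 × 0.2 × 15² = 536. Control: 0.8 × 625 = 500.
- Carried forward, 71 per arm: √(1036 / 71 × 1.28) = 4.32.
- Observed only, 0.8 × 71 = 56.8 per arm: 25 × √(2 / 56.8 × 1.28) = 5.31.
- No missing data, 71 per arm: 25 × √(2 / 71 × 1.28) = 4.75.
- Carried forward to observed: 4.32 / 5.31 = 0.81. The ratio is 0.81 to 0.82 for correlations of 0.3 to 0.7.
- Effect over SE: 12 / 4.32 = 2.78, against 15 / 5.31 = 2.83.

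**Simulation at 12 months.** 20 centres of 7 caregivers, ICC 0.02, SD 25, correlation 0.5, 1500 runs per scenario. The correlation, the course over time and the pattern of loss are assumptions. The reference column is the mean estimate with no data missing.

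| Scenario | Reference | Last carried forward | Baseline carried forward |
|---|---|---|---|
| Constant effect 15, random loss 20% in each arm | 15.0 | 14.0 | 12.1 |
| Effect fading 15/10/5, random loss 20% in each arm | 5.0 | 5.7 | 4.1 |
| Fading effect, control declining, informative loss 32% intervention, 21% control | 5.1 | 7.3 | 4.8 |
| No effect, both arms declining, informative loss 40% intervention, 21% control | 0.0 | +1.8 | +1.9 |
| No effect, both arms declining, informative loss 18% intervention, 35% control | 0.0 | −1.8 | −2.0 |
| No effect, random loss 20% in each arm | 0.1 | 0.1 | 0.1 |

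The largest bias of the last-value rule in any scenario run was 2.9 points (12.3 against 15.2), with a constant effect, a declining control arm and informative loss of 12% intervention and 35% control. Several unequal-loss scenarios assume more overall loss than the planned 20%.

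In the first scenario the average reported SE, ignoring clustering, was 4.1 for last carried forward and 3.8 for baseline carried forward, against 4.7 for observed cases and 4.2 with complete data.

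**The case against.** Much can be said for the plan, and part of it stands.

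- A reader might infer that the confidence interval is too narrow whatever happens. The figures do not show that. 4.32 is about the true sampling error of the carried-forward statistic, because the imputed zeros shrink the estimate and its SE together. With equal loss the test is almost unchanged (2.78 against 2.83). The narrower fault remains: imputed values count as observed information about a shrunken quantity.
- A reader might infer that the rule contradicts the sample size. It does not. Recruiting extra caregivers to allow for loss is compatible with imputing in an intention-to-treat analysis.
- A reader might infer that two rival primary results are licensed. The wording can also be read as one rule: the last value where a follow-up value exists, baseline where none does. It is unclear, but clarification would settle it.
- The 12 points apply only if baseline is carried forward for the whole 20%. That figure is for one year, and loss accrued by earlier visits cannot exceed it. For the last-value rule the bias is small beside an SE of 4 to 5.
- Causes of loss are recorded, visits are arranged by phone, and those who leave are described. This helps interpretation but leaves the estimate as it is.
- A mixed model valid under missing at random does not remove bias from informative loss. That is correct, and is why the remedy needs a sensitivity analysis.

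**Conclusion.** The concern holds in limited form and should be fixed. The only stated handling of missing VAS values assumes no change after events that, on the protocol's own account, are likely to change the caregiver's rating.

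The clearest consequence is for baseline carried forward: 15 becomes 12 with 20% loss in each arm, if the effect in those lost equals that in completers. A treatment that truly met the 15-point hypothesis would then be estimated below it on average. The reported SE would also be smaller than that of a trial with no missing data (4.32 against 4.75).

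For last observation carried forward the bias is usually smaller and its direction cannot be stated in advance. It was roughly 1 to 2 points in most of the unfavourable scenarios and close to 3 in one, all resting on assumed loss patterns. With equal loss and no true effect there is essentially no bias, so the documents do not support a claim that the plan will produce a false positive result.

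**What to change.** Replace the carry-forward sentence in the Analysis section with text such as: *The primary analysis is a likelihood-based mixed model for repeated measures fitted to all observed VAS values at baseline and at 0, 6 and 12 months after the intervention. Baseline is part of the outcome vector, health centre is a random effect, and no value is singly imputed. The analysis is valid under missing at random.*

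With baseline in the outcome vector, every randomised caregiver with at least one VAS value is kept, which respects the intention-to-treat statement. The centre effect is needed because centres are randomised, and the Discussion already intends models that allow for intracluster correlation.

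Then add:
- a delta-adjusted multiple imputation that respects clustering, with the range of deltas fixed in advance, because loss may be informative;
- carry-forward as a sensitivity analysis only, with a stated rule for when the last value applies and when baseline does;
- a sentence on whether the VAS after the dependent patient's death is part of the question, since the choice of delta depends on it.

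The cost is a few sentences, one more analysis and a somewhat wider confidence interval. A mixed-effects model is already planned, and the sample size stays at 142 because it already allows for 20% loss.
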